## **14.0 QUALITY CONTROL AND QUALITY ASSURANCE**

In order to assure quality of the clinical and surgical procedures, the following has or will be done:

- The sites were chosen based on their current knowledge and experience performing conventional male circumcisions in adults, adolescents and younger boys. Additionally, the Homa Bay site has previous experience conducting numerous conventional circumcision outreaches that involve all age groups, one major conventional circumcision study and five clinical studies on the Shang Ring;
- Those male circumcision providers who have not previously used the Shang Ring will be trained locally by EngenderHealth, Cornell and Homa Bay County Hospital staff experienced with use of the Shang Ring;
- All study staff who are not current with research ethics and GCP training will be trained before the start of the study; and,
- The study will be conducted in compliance with the protocol, evolving SOPs, and GCP.

The study sites will maintain all source documents used to complete electronic CRFs, including medical chart notes, laboratory reports, and documentation of referrals, and allow the monitors and other authorized individuals will have access to study documents and pertinent medical records. The study sites may be asked to send copies of some source documentation, with participant identifiers expunged, as well as administrative documentation to EngenderHealth or Weill Cornell Medical College for review.

The investigators and study sites may be subject to a field audit by the sponsor or regulatory agencies to validate the participation of study participants and to verify the

data reported on the eCRFs. This audit could occur while the study is still in progress, several years after the study is completed, or when the data are under review by a regulatory agency. All of the participants' records and other study documentation must be filed and accessible on short notice (three to five working days) during the study and subsequent retention period. Documentation of the study will be adequate for reconstruction of the course of events.

Throughout the study period and after study completion, participant files should be stored in locked file cabinets with access limited to study staff for a minimum of five (5) years.

## **15.0 SUMMARY OF STUDY MONITORING**

During the course of this study, an appropriately trained clinical monitor will maintain regular contact with the study sites and will conduct periodic on-site monitoring visits as needed and as feasible, including visits for training (e.g. research ethics, GCP, study specific), interim monitoring and close-out. The purpose of these visits is to assure that the study is being conducted and informed consent is being obtained according to the approved protocol, GCP, and applicable regulatory guidelines, and to monitor recruitment and data quality.

While some eCRFs may serve as source documents, all documents or records that will serve as source documentation for this study will be fully outlined in the study manual.

Surgical monitoring will be under the purview of Weill Cornell Medical Center and EngenderHealth. Trained surgeons will participate in training activities and regularly monitor the site to assess adherence to acceptable standard of practice and surgical procedures.

## **16.0 PUBLICATION AND PRESENTATION OF RESULTS**

Any and all publications about the study will be developed collaboratively with EngenderHealth, Weill Cornell Medical College and the other study investigators. Furthermore, any presentations/publications about the study results will assign proper credit and acknowledgement to the contributions of the Kenya Ministry of Health, National AIDS/STI Control Programme (NASCOP), Homa Bay County Hospital, Vipingo Health Center, EngenderHealth, and Weill Cornell Medical College.

Subsequently, secondary analysis may be undertaken by either EngenderHealth or Weill Cornell Medical College who have the capability to utilize the data properly and professionally.

No data collected in this study may be published without prior written agreement between EngenderHealth, and Weill Cornell Medical College.

The study will be registered on ClinicalTrials.gov before it begins.

## **17.0 ACKNOWLEDGMENTS**

The PEC thanks the Bill & Melinda Gates Foundation who are funding this study, [name] for her guidance and technical insight, and our local partners in Kenya, the Ministry of Health, the National AIDS & STI Control Programme (NASCOP), the Homa Bay County Hospital and Health Management Team (who have facilitated previous studies and trainings on the Shang ring as a device for use in adult male circumcision) and the Kilifi County Health Management team.

# 18.0 APPENDIXES

## Appendix I: Shang Ring circumcision procedure

|                                           | Standard Technique                                                                                                          | No-flip Technique                                                                                                           |
|-------------------------------------------|-----------------------------------------------------------------------------------------------------------------------------|-----------------------------------------------------------------------------------------------------------------------------|
| 1. Measure                                | [figure not shown]                                           | Penis measured to determine Shang Ring size in the same way as for standard technique                                       |
| 2. Place the inner ring                   | [figure not shown]
Inner ring placed outside the foreskin | [figure not shown]
Inner ring placed inside the foreskin |
| 3. Evert the foreskin over the inner ring | [figure not shown]                                         | Foreskin does not need to be everted when using the no-flip technique                                                       |
| 4. Place the outer ring                   | [figure not shown]                                         | [figure not shown]                                        |
| 5. Cut off the foreskin                   | [figure not shown]                                         | [figure not shown]                                        |

## Appendix II: Shang Ring removal procedure

|                                          |                                                                                      |
|------------------------------------------|--------------------------------------------------------------------------------------|
| 1. Open the inner ring with lock opener  | [figure not shown]   |
| 2. Separate dry scub from the inner ring | [figure not shown]  |
| 3. Cut off the inner ring                | [figure not shown] |
| 4. Apply bandage around the wound        | [figure not shown] |

[figure not shown]

---

# DNV BUSINESS ASSURANCE

---

## EC CERTIFICATE - FULL QUALITY ASSURANCE SYSTEM

---

Certificate No. 4888-2014-CE-RGC-NA  
This Certificate consists of 3 pages

*This is to certify that the Quality Management System of*

**Wuhu SNDA Medical Treatment Appliance Technology Co., Ltd.**

P.R. China

*for design, production and final product inspection/testing of*

**Disposable Micro-injury Peritomy Anastomosis Devices**

*has been assessed with respect to*

the conformity assessment procedure described in Article 11.3.a and Annex II excluding section 4 (Module H) of Council Directive 93/42/EEC on Medical Devices, as amended, and found to comply

*Further details are given overleaf*

*Place and date:*

Høvik, 01 December 2014

For DNV GL BUSINESS ASSURANCE  
NORWAY AS

[figure not shown][figure not shown]

Notified Body No.:  
0434

*This Certificate is valid until:*

### Terms and conditions

The certificate is subject to the following terms and conditions:

- Any producer (see 2001/95/EC for a precise definition) is liable for damage caused by a defect in his product(s), in accordance with directive 85/374/EEC, as amended, concerning liability of defective products.
- The certificate is only valid for the products and/or manufacturing premises listed above.
- The Manufacturer shall fulfil the obligations arising out of the quality system as approved and uphold it so that it remains adequate and efficient.
- The Manufacturer shall inform the local DNV Office of any intended updating of the quality system and DNV will assess the changes and decide if the certificate remains valid.
- Periodical audits will be held, in order to verify that the Manufacturer maintains and applies the quality system DNV reserves the right, on a spot basis or based on suspicion, to pay unannounced visits.

The following may render this Certificate invalid:

- Changes in the quality system affecting production.
- Periodical audits not held within the allowed time window.

### Conformity declaration and marking of product

When meeting with the terms and conditions above, the producer may draw up an EC declaration of conformity and legally affix the CE mark followed by the Notified Body identification number of DNV.

END OF CERTIFICATE

## Appendix IV: EN ISO certificate

[figure not shown]

# CERTIFICATE OF REGISTRATION

This is to certify that

**Wuhu Snnda Medical Treatment Appliance Technology Co., Ltd.**  
[name]  
[name]

operates a

## Quality Management System

which complies with the requirements of

## SAI GLOBAL

INFORM. INSPIRE. IMPROVE.

[figure not shown]

# DNV BUSINESS ASSURANCE MANAGEMENT SYSTEM CERTIFICATE

Certificate No. 111795-2012-AQ-RGC-NA

*This is to certify that the Management System of:*

**Wuhu SNNDA Medical Treatment Appliance Technology Co., Ltd.**

**[name]  
[name]**

*has been found to conform to the standard:*

## **Appendix V: Culture sub-study**

### **Background**

The objective of this sub-study is to increase the knowledge regarding the bacterial micro-environment that patients undergoing circumcision face. The WHO has recently reported on a number of tetanus-related deaths in patients undergoing male circumcision in Africa. As such, there has been a corresponding interest in trying to understand the microbiome that exists on the penis at the time of circumcision as well as afterwards during the healing process. We will collaborate with the Rakai Health Sciences Project based in Uganda which has significant experience in male circumcision, using both conventional as well as device-driven technique. Our samples will be compiled and genetically analyzed to assess the spectrum of microbes that exist. The data will inform policy makers regarding the need for standard tetanus immunization, the need for antibiotic prophylaxis and patient preparation techniques for circumcision.

A subset of participants in the main study will be asked if they are interested in participating in this sub-study and if so, will be consented for the sub-study using the sub-study specific consent and assent forms, following the same procedures as for the main study. We plan to enroll 50 participants in the culture sub-study.

### **Sample Collection**

We shall collect one flocked swab for microbiome analysis that is pre-moistened with sterile normal saline, placed immediately in 1ml of sterile phosphate buffer saline (PBS), and stored at 4°C until transferred to -80°C within 24 hours. Swabs will be stored at -80°C until processing and analysis.

AT ALL TIME POINTS SWABS SHOULD BE TAKEN BEFORE THE PENIS IS WIPED WITH BETADINE OR ANY OTHER ANTISPETIC PRODUCT.

- Pre-Op: Pre-moisten the swab with sterile normal saline. Swab under the foreskin at the coronal sulcus prior to surgery, rotating swab at least two times in a non-traumatic manner. This swab should be labeled with the participant's number and "pre-op coronal sulcus microbiome".
- At week 1 post-MC: The sample should be collected before the ring is removed. Pre-moisten the swab with sterile normal saline. Rotating swab at least two times around the surface where the ring meets the penis along the top and bottom of the ring. This swab should be labeled with the participant's number and "week 1 post-MC coronal sulcus microbiome".
- At week-6 post-MC: Pre-moisten the swab with sterile normal saline. Rotate the swab at least two times around the coronal sulcus in a non-traumatic manner. This swab should be labeled with the participant's number and "week 6 post-MC coronal sulcus microbiome".

## **Microbiome Analysis**

Swabs will be processed by the Translational Genomics Research Institute in Arizona, USA. This is the same lab that has processed the samples collected from men undergoing circumcision in the Rakai Health Sciences Project in Uganda.

*Cell lysis and DNA isolation:* We will extract total DNA using 100ul of swab eluent in an enzyme-free combination of chemical and mechanical lysis, followed by DNA purification using the Qiagen AllPrep Kit according to manufacturer's instruction.

*Microbiome characterization:* Using the total DNA, we will characterize penile microbiota using pan-bacterial quantitative real-time PCR and 16S rRNA gene-based sequencing analysis, as previously described (PMID 25058515, 22510143). We will use an in-house custom pipeline to process and generate taxonomic classification of the resultant sequences. Combining the qPCR and sequencing results, we will generate proportional and absolute abundance matrices for ecological analysis.

*Ecological analysis:* We will examine the change in penile bacterial absolute abundance and in total penile anaerobes from pre-op to at week 6 post-MC using Wilcoxon Ranked-sum Test. We will assess the change in prevalence, proportional abundance, and absolute abundance of each penile bacterium. We will visualize the penile microbiota using heat-map and non-metric dimensional analysis.

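### The only named microbiome test treats pre-op and week-6 swabs from the same participants as independent groups, and no contrast or test is specified for the week-1 swab taken with the ring on

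*Combined protocol and SAP*

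**What the plan says.** Appendix V (Culture sub-study), Background, describes an interest in "the microbiome that exists on the penis at the time of circumcision as well as afterwards during the healing process". It states a descriptive aim, "Our samples will be compiled and genetically analyzed to assess the spectrum of microbes that exist", and a size: "We plan to enroll 50 participants in the culture sub-study". It gives no hypothesis, significance level or power.

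Appendix V, Sample Collection, sets three swabs per participant, each labelled with the participant's number:

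- **Pre-op:** "Swab under the foreskin at the coronal sulcus prior to surgery, rotating swab at least two times in a non-traumatic manner".
- **Week 1:** "The sample should be collected before the ring is removed". The surface differs: "Rotating swab at least two times around the surface where the ring meets the penis along the top and bottom of the ring".
- **Week 6:** coronal sulcus again.

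Appendix V, Microbiome Analysis, names one test. It applies to the change in bacterial absolute abundance and "in total penile anaerobes from pre-op to at week 6 post-MC using Wilcoxon Ranked-sum Test". The two sentences that follow plan an assessment of change for each bacterium (prevalence, proportional and absolute abundance) and a heat-map with ordination. Neither names a time point or a test.

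Section 9.2 (Analysis Plan Summary) covers the trial endpoints with between-group t-tests and chi-squared tests. It supplies no within-participant microbiome analysis.

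**The concern.** There are two separate gaps.

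First, the named test does not fit the data. The question is change within a participant from one time to another, and each participant supplies both swabs. A rank-sum test compares two unrelated samples, so it leaves the stable differences between participants in the error term. The likely cost is missed change in a sample of only 50, not false positives.

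Second, the only swab taken with the ring in place appears in no stated contrast. The sub-study is meant to inform policy on tetanus immunization, antibiotic prophylaxis and patient preparation, and its interest includes the healing period. If anaerobes rose at week 1 and returned to the pre-op level by week 6, the one named test would not show it. How week 1 is summarised would then be decided after the data are seen.

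**Working it through.** The documents give no power, significance level or within-participant correlation for the sub-study, so there is no stated figure to reproduce. The checks below use the documents' numbers where they exist and marked assumptions elsewhere.

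**1. Is the named comparison paired?** Yes. Sample Collection takes all three swabs from the same participant under one participant number. With 50 planned, that is 50 × 3 = 150 swabs. The named test uses the 50 pre-op and 50 week-6 swabs as if they came from 100 different people.

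**2. Effect of ignoring the pairing.** Let each swab measure have variance σ² and let swabs from one participant have correlation r.

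- Variance assumed by an independent-groups comparison of means: 2σ²/n.
- Actual variance of the mean change: 2σ²(1 − r)/n.
- Ratio: 1/(1 − r).

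The values of r are assumed. Suppose, as an illustration, that the correct paired test has 80% power at two-sided 0.05. The true change is then 1.960 + 0.842 = 2.802 paired standard errors. The unpaired test rejects only beyond c = 1.960/√(1 − r) of those standard errors. Its true false-positive rate is 2Φ(−c), and its power is about Φ(2.802 − c).

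| Assumed r | Variance ratio | SE ratio | c | False-positive rate | Power |
|---|---|---|---|---|---|
| 0.3 | 1.43 | 1.20 | 2.343 | 0.019 | 68% |
| 0.5 | 2.00 | 1.41 | 2.772 | 0.006 | 51% |
| 0.7 | 3.33 | 1.83 | 3.578 | 0.0003 | 22% |

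These are results for means under normality with equal variances. For rank tests they show direction and rough size only.

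**3. What state is the wound in at each post-operative swab?** The Summary places the microbiome study in Phase II, where Section 8.3 removes every ring at day 7. Week 1 is therefore the only scheduled swab with the ring on. Section 1.3.2 gives mean healing times of 44.1 ± 12.6 days (adult Shang Ring arm of the randomized comparison with conventional surgery) and 29.9 ± 7.3 days (Kenyan pilot in boys). Using a normal approximation:

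- Day 7, adults: z = (7 − 44.1)/12.6 = −2.94, so 99.8% unhealed.
- Day 7, boys: z = (7 − 29.9)/7.3 = −3.14, so 99.9% unhealed.
- Day 42, adults: z = (42 − 44.1)/12.6 = −0.17, so about 57% unhealed.
- Day 42, boys: z = (42 − 29.9)/7.3 = 1.66, so about 5% unhealed.
- Field study, observed at the 35–42 day visit: 90.5% and 91.3% healed, so 9.5% and 8.7% unhealed.

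Week 1 reliably samples an unhealed wound. Week 6 samples a mixture whose make-up depends on which source applies.

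**4. What would a paired week-1 contrast cost?** Assume 50 complete pairs and 80% power. The detectable change, in SDs of the within-participant difference, is (z for α + 0.842)/√50.

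- Two-sided 0.05: 2.802/7.071 = 0.40, or 0.41 for signed-rank (dividing by √0.955, its relative efficiency under normality).
- Two-sided 0.025, if α is split over two contrasts: (2.241 + 0.842)/7.071 = 0.44, or 0.45 for signed-rank.

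**The case against.** The strongest reply is that the sub-study is descriptive. It sets out to catalogue bacteria, states no hypothesis, and can describe the week-1 flora without any test. The per-bacterium and visual analyses name no time points, so week 1 may well enter them. This stands. A reader might infer that the week-1 swab is discarded, or that the sub-study cannot address healing at all. The documents do not support either reading: the use of week 1 is unspecified, not ruled out.

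A related inference is that week 6 falls wholly after healing, so that the named contrast says nothing about the wound. The documents' own figures put the unhealed share at day 42 anywhere from about 5% to 57%, so that is too strong as well.

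There is also a plausible reason for choosing pre-op against week 6, though the plan does not give it. Both swabs come from the coronal sulcus, whereas the week-1 swab is taken where the ring meets the penis, even though its label says coronal sulcus. A week-1 contrast mixes time with sampling surface, and nothing in the documents requires it to rank first. This stands and shapes the fix.

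Finally, the test name may be loose wording for the signed-rank test, since it is attached to a change over time. That is possible, but the text as written names the independent-samples test and no other section corrects it.

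**Conclusion.** The point holds as a minor one. The pairing error is clear from the text: the one named test assumes independent groups, and the swabs it compares come from the same 50 planned participants. With positive within-participant correlation the result is an overstated standard error and lost power. The variance is about 1.4 to 3.3 times too large for r of 0.3 to 0.7, where r is assumed and the formula is only a guide for rank tests. A reader might take this as a risk of spurious findings; with positive correlation the error runs the other way.

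The week-1 gap is one of specification. The only ring-on swab has no stated contrast or test, although healing is part of what the sub-study set out to understand. The conclusion does not depend on how many wounds are open at week 6.

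**What to change.** In Appendix V, Microbiome Analysis:

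1. Replace the rank-sum test with the Wilcoxon signed-rank test for pre-op against week 6, or use a mixed model with a participant effect over the three times.
2. Add a paired pre-op against week-1 contrast on the same two outcomes, total absolute abundance and total anaerobes. State beside it that the week-1 swab samples the ring–penis interface rather than the coronal sulcus, so time and surface cannot be separated in that contrast.
3. Name the time points used in the per-bacterium and visual analyses.

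If the investigators prefer to keep week 1 purely descriptive, saying so would also close that gap.

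The cost is wording. All three swabs are already scheduled, so no new swabs or visits are needed. The small downside is a second exploratory comparison. If α were split over the two, the detectable change would move from about 0.40 to 0.44 SD of the within-participant difference, under the assumptions shown in the working.

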All other endpoints will be summarized by anesthetic technique and compared between groups using either two-sample t-tests or chi-squared tests, as appropriate for the endpoint, all conducted at the two-sided 0.05 significance level. We will not make any adjustments for multiple comparisons. 95% confidence intervals for differences between groups will be presented. Missing data will be assumed to be missing in random fashion and ignored.

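### Appendix V names the Wilcoxon rank-sum test, a test for independent samples, for a paired pre-op to week-6 comparison; it ignores the pairing and may cost power, depending on a correlation that the plan does not give

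*Combined protocol and SAP*

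**What the plan says.** Appendix V, Background, sets the size: "We plan to enroll 50 participants in the culture sub-study". Sample Collection takes swabs from the same participant at three times: before surgery, at week 1 and at week 6. The pre-op instruction is "Swab under the foreskin at the coronal sulcus prior to surgery, rotating swab at least two times in a non-traumatic manner". The week-6 instruction is "Rotate the swab at least two times around the coronal sulcus in a non-traumatic manner". At each time, "This swab should be labeled with the participant's number", so the swabs can be matched.

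Microbiome Analysis then states the question as one of change: "We will examine the change in penile bacterial absolute abundance", together with "total penile anaerobes from pre-op to at week 6 post-MC using Wilcoxon Ranked-sum Test". No paired test is named anywhere in the appendix. It gives no significance level, expected change, SD, within-person correlation, or reason for choosing 50. Section 9.2 promises a detailed analysis plan, which is not among the documents, and its summary of analyses covers the two phases without mentioning the sub-study.

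**The concern.** The rank-sum test compares two unrelated groups. Here the two sets of values come from the same people, and the appendix describes no comparison of independent groups to which the test could apply. Run as written, it would treat 50 linked pairs as 100 independent swabs and discard the participant link that the labelling preserves.

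The consequence depends on how alike a participant's two swabs are. If they are positively correlated, the test overstates the variance of the difference, rejects too seldom under no change, and can miss a moderate change that a paired test would detect. If they are negatively correlated, it rejects too often. At stake is how the pre-op to week-6 result of the sub-study is read: a non-significant result could reflect the test rather than the data.

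**Working it through.** **No figure to reproduce.** The plan gives no power or detectable change for the sub-study, so the check is of the test itself.

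**Inputs from the documents.** There are 50 participants (Appendix V, Background), hence at most 50 pairs. The level is not stated for the sub-study; two-sided 0.05 is borrowed from section 9.2 ("all conducted at the two-sided 0.05 significance level").

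**Assumed inputs.** Within-person correlation ρ from -0.2 to 0.7, a shift of 0, 0.4 or 0.8 SD, and bivariate normal data on a transformed scale with equal SDs.

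**Approximation.** With rank efficiency 3/π, the standard error of the shift in SD units is:

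- assumed by rank-sum: √[(2/50)/(3/π)] = √(0.04/0.9549) = 0.205
- true for paired data: 0.205 × √(1-ρ)

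The actual rejection rate of rank-sum under no change is therefore about 2 × [1 - Φ(1.96/√(1-ρ))]:

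- ρ = -0.2: 1.96/1.095 = 1.79, giving 7.4%
- ρ = 0: 5.0%
- ρ = 0.2: 1.96/0.894 = 2.19, giving 2.8%
- ρ = 0.3: 1.9%
- ρ = 0.5: 0.6%

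The shift detectable with 80% power is 1.96 × 0.205 + 0.84 × (true SE) for rank-sum and 2.80 × (true SE) for signed-rank. In SD units, rank-sum against signed-rank:

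- ρ = 0: 0.57 against 0.57
- ρ = 0.3: 0.55 against 0.48
- ρ = 0.5: 0.52 against 0.41
- ρ = 0.7: 0.50 against 0.31

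**Simulation.** 10,000 replicates per cell, 50 pairs, two-sided 0.05. Each cell shows rank-sum / signed-rank, in per cent.

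| ρ | Rejection, no change | Power, 0.4 SD | Power, 0.8 SD |
|---|---|---|---|
| -0.2 | 7.4 / 5.4 | 49.8 / 42.4 | 96.3 / 94.1 |
| 0 | 4.8 / 4.8 | 49.4 / 48.9 | 97.0 / 96.7 |
| 0.2 | 3.0 / 4.7 | 49.0 / 57.0 | 98.2 / 98.9 |
| 0.3 | 2.0 / 4.9 | 49.0 / 63.0 | 98.7 / 99.6 |
| 0.5 | 0.8 / 4.8 | 49.5 / 78.1 | 99.6 / 100 |
| 0.7 | 0.1 / 4.8 | 48.9 / 93.4 | 100 / 100 |

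The simulation standard error is at most √(0.25/10,000) = 0.5 points. Rank-sum power at 0.4 SD stays near 49% whatever ρ is because its critical shift, 1.96 × 0.205 = 0.40 SD, happens to equal the shift assumed. At ρ = -0.2 the higher rank-sum power is not a real gain, since it comes with a 7.4% error rate.

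**Missing week-6 swabs.** The appendix states no attrition. Section 9.1 expects complete data on 300 of 345 in Phase II. The same rate gives 50 × 300/345 = 43.5, so about 43 pairs. At 43 pairs, ρ = 0.5 and 0.4 SD, power is 40% for rank-sum and 71% for signed-rank: the same pattern.

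**The case against.** The strongest reply is that the loss of power is not established, and this stands. It is nil if the swabs are uncorrelated, about 8 points at correlation 0.2 with a 0.4 SD shift, and at most about 1 point at 0.8 SD for correlations from 0 upwards. A high correlation cannot be taken for granted: the pre-op swab is taken under the foreskin, the week-6 swab after the foreskin has been removed, so the sampled site has changed. A reader might infer that much of the information from 50 participants will be lost, or that real changes will be missed. The documents give neither the correlation nor the shift, so they do not support either statement. The normal model is also an assumption.

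A reader might also infer that policy on immunization or prophylaxis is at risk. The Background section does say that the data will inform policy makers, but the Summary presents the microbiome study as descriptive, and no decision is tied to this p-value.

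The wording may be a slip for signed-rank, since the text speaks of change. That is possible, and the detailed plan promised in section 9.2 might settle it. But an analyst following Appendix V as written would run the wrong test, and nothing available corrects it.

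Finally, one might add a paired test for the prevalence of each bacterium and control of the false discovery rate. The appendix names no test for those analyses, so such additions would fill in unstated detail rather than correct this error. They are not part of this point.

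**Conclusion.** The test named does not fit the design: it is for independent samples, and the comparison is within participants on linked swabs. This follows from the text alone. The size of the effect is conditional. Under bivariate normal data with 50 pairs, the nominal 5% level becomes about 3, 2 and 1% at correlations 0.2, 0.3 and 0.5, and about 7% at -0.2. At a 0.4 SD shift the power given up runs from none at correlation 0 to about 8 points at 0.2, 29 at 0.5 and 45 at 0.7. Which of these applies cannot be determined from the documents. The correction is minor: it concerns a sub-study and leaves the Phase I and Phase II primary endpoints untouched.

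**What to change.** In Appendix V, Microbiome Analysis, replace the rank-sum test with the Wilcoxon signed-rank test on each participant's pre-op to week-6 difference, for total absolute abundance and for total anaerobes. State that the analysis uses participants with both swabs, and report the number of complete pairs.

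The cost is a sentence or two of text. No new data, swabs or participants are needed. If the swabs prove uncorrelated, little is given up: at correlation 0 the two tests differ in power by half a point or less at the shifts tabulated.
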